### Statistical procedures

#### Sample size

Given the absence of exercise interventions for patients with persistent COVID-19 symptoms [57], in this area, a conservative approach will be used to estimate the sample size. Inspired by a Lau et al. study [58], it is expected that the exercise group will increase cardiorespiratory fitness at least 1-MET (3.5 mL/kg/min) more than the standard care group with an SD of 5.4%. A sample size of 84 participants (42 per group) provides statistical power (1−*β*) of 80% using a two-tailed alpha <0.05 and adjustment for baseline value and other prognostic covariates [59]. This sample size will also be sufficient for detecting differences in our secondary biomarkers and patient-reported outcomes. Considering a potential dropout rate of <15–20% based on our previous exercise trials [60, 61], a total of 100 participants (50 per group) will be randomized. This power will also be sufficient for detecting differences in our secondary biomarkers and patient-reported outcomes if the effects are moderate (i.e., effect size of Cohen’s *d* ≥ 0.6). This power is not sufficient for detecting potentially meaningful differences in any of the exploratory clinical outcomes. Given that the purpose of this phase II trial is to inform larger phase II and III trials, the patient-reported and clinical outcomes will also be interpreted for potential clinical significance based on the direction and magnitude of numerical differences. These calculations were performed with the Power and Sample Size Calculations program, Version 2.1.23.

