### Isolating the peripheral blood mononuclear cells (PBMCs) and metabolomic analysis

A random subsample of participants (20 subjects in each group, *n*=40) will be included to isolate the PBMCs by Ficoll gradient, as previously described [41]. The following fluorochrome-conjugated antibodies will be used: CD4, CD8, PD1, CD62L, KLRG1, CD28, CD57, CD163, CD119, CD56, CD116, CD66b, CD11b, and CD14. Cells will be washed, stained and analyzed by flow cytometry. In addition, plasma lipid extraction will be performed and then analyzed by ultrahigh-resolution liquid chromatography coupled to mass spectrometry (UHPLC–MS) using ultrahigh-resolution liquid chromatography coupled to mass spectrometry (UHPLC–MS) using the technique described by Barr et al. [42]. In summary, plasma lipid extraction is a liquid extraction of the serum with chloroform/methanol (2:1) and a saline solution of sodium chloride followed by incubation the mixture for 1 h at −20 °C to promote the precipitation of proteins. Next, the sample is evaporated in an evaporating concentrator, and the dry extract is reconstituted in acetonitrile/isopropanol. After centrifugation, the supernatant is analyzed by UHPLC–MS. For this purpose, the chromatographic column UPLC BEH C18, 2. 1×100 mm, 1.7 μm (Waters Corp. Milford, MA, USA) will be used, with a mobile phase consisting of a binary mixture formed by H_2_O/acetonitrile/10 mM ammonium formate and acetonitrile/isopropanol/10 mM ammonium formate. The conditions of chromatographic separation and high-resolution mass spectrometry (Xevo G2 QToF, Waters Corp.) have been previously described [43].

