## Discussion

The present study will investigate the modification in immunological parameters, physical condition, inflammatory profile, and changes in perceived persistent symptoms (fatigue/tiredness, musculoskeletal pain, shortness of breath) after 6 weeks of multicomponent and supervised physical exercise in addition to the standard medical treatment scheme in patients with persistent COVID-19 symptoms. Recent experimental evidence has shown that skeletal muscle is capable of modifying low-grade subclinical inflammation and modulating the immune system and endocannabinoids. The EXER-COVID Crossover Study is a radical innovation that explores the possibility of reducing the degree of perception of persistent symptoms. Specifically, the primary purpose of this proposal is to implement precision exercise medicine that modulates the immune system, physical condition, and inflammation. The EXER-COVID Crossover Study is expected, based on the knowledge and cutting-edge developments provided by different researchers, to offer a nonpharmacological intervention that provides personalized management of the persistent symptoms of COVID-19. Since we will provide preliminary insights into the effect of a multicomponent exercise program on immunological parameters, physical condition, inflammatory profile, and persistent perceived symptoms, the results obtained should be of special interest for the design of health promotion and prevention programs for patients with persistent COVID-19 symptoms at the national and international levels. We expect that the information obtained by this study will inform future guidelines on the exercise training rehabilitation of patients with postdischarge symptoms after COVID-19.

Interestingly, by using a crossover trial, we minimize the risk of confounding because all interventions are measured on the same participants. One can say that study participants serve as their own control. This is achieved via computing the treatment effects separately in two sequence groups formed via randomization. Another advantage which is less study participants is required than parallel-group trials to meet the same criteria in terms of type I and type II error risks, when studying new interventions [63].

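### The sample-size statement cannot be reproduced from its own inputs (SD in per cent, effect in mL/kg/min) and is worked for two independent groups, not for the planned crossover test

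*Protocol article*

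**What the plan says.** All the inputs are in the Sample size section of the protocol article.

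- **Effect:** the exercise group is expected to gain at least "1-MET (3.5 mL/kg/min) more than the standard care group with an SD of 5.4".
- **SD:** that 5.4 is printed with a per cent sign. No base is given, and the text does not say whether it is the SD of the value, of the change or of the within-person difference.
- **Size and power:** "A sample size of 84 participants (42 per group) provides statistical power" "of 80% using a two-tailed alpha <0.05". The same sentence invokes adjustment for baseline and other prognostic covariates, but gives no correlation or R-squared.
- **Dropout:** "Considering a potential dropout rate of <15–20% based on our previous exercise trials", leading to 100 randomised, 50 per group.
- **Secondary outcomes:** power is called sufficient, at first without condition and then for Cohen's d of at least 0.6.

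The design is described elsewhere. The Procedure section has every participant complete both conditions. The section on non-adherence and missing data plans a crossover analysis by t tests or ANOVA with participants as blocking factors. The Discussion notes as an advantage of crossover designs that "less study participants is required than parallel-group trials to meet the same criteria in terms of type I and type II error risks".

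**The concern.** The paragraph is the only justification given for randomising 100 people, and it fails in three ways. Its effect and its SD are in different units. Its sample size does not follow from its stated alpha, power, effect and SD. It has the form of a comparison of two independent groups, while the planned test compares each participant with himself or herself. The dropout allowance also falls short of the top of its own range.

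At stake is what the stated 80% means. A reader facing a null result for the primary outcome, V̇O2max, could not tell from this paragraph which differences the planned analysis was able to detect.

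**Working it through.** **Inputs from the Sample size section:** difference 3.5 mL/kg/min; SD 5.4 (unit in doubt); two-sided alpha 0.05; power 80%; 42 per group; 100 randomised; dropout under 15–20%. Every correlation and every baseline V̇O2max below is an assumption, because the article gives none.

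**1. The plan's own figure, with 5.4 read as mL/kg/min.** d = 3.5/5.4 = 0.648. By normal approximation, n per group = 2 × (1.960 + 0.842)² × (5.4/3.5)² = 37.4, so 38. With the noncentral t, 39. At 42 per group the power is 83.5% (t) or 84.4% (normal). The stated pair of 42 and 80% is not reproduced. To get exactly 80% at 42 per group, the SD would have to be about 5.66 (t) or 5.72 (normal).

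**2. 5.4 read as a percentage of V̇O2max.** For an assumed baseline of 15 to 40 mL/kg/min, the SD is 0.054 × 15 = 0.81 to 0.054 × 40 = 2.16. The t test then needs 3 to 8 per group, and power at 42 is practically 100%.

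**3. Baseline adjustment.** Multiplying 37.4 by (1 − ρ²) gives 35 per group at ρ = 0.3 and 29 at ρ = 0.5. The adjustment that the sentence invokes moves the answer further from 42.

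**4. Routes that do reach 42.** If 5.4 is the SD of the raw value and change scores are compared, the SD of the change is 5.4 × √(2(1 − ρ)). At ρ = 0.44 this is 5.71, and n = 41.9 by normal approximation, so 42. The article states no such correlation. One-sided 0.05 with 90% power also gives 42 (t), but contradicts the stated two-sided 80%.

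**5. The planned crossover test.** SD of the within-person difference = 5.4 × √(2(1 − ρ)), with 84 completers, 82 degrees of freedom and no carryover.

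| Within-person ρ (assumed) | SD of difference | Noncentrality 3.5√84/SD | Power |
|---|---|---|---|
| 0 | 7.64 | 4.20 | 98.6% |
| 0.5 | 5.40 | 5.94 | over 99.9% |

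**6. Dropout.** 1 − 84/100 = 16%. Keeping 84 completers needs 84/0.85 = 98.8, so 99 randomised, at 15% loss, and 84/0.80 = 105 at 20%. At 20% loss, 100 leave 80, or 40 per group. A two-group test with SD 5.4 mL/kg/min then has 81.7% power. If 42 per group is taken to give exactly 80%, as the plan states, 40 per group give 78.0%.

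**7. Secondary outcomes, on the same two-group basis.** At d = 0.6, 42 per group give 77.6% power, and 80% needs 45 per group. With 42 per group, 80% power needs d of about 0.62.

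**The case against.** The strongest reply is that nothing here endangers the trial. If 5.4 is mL/kg/min, the discrepancy is 39 against 42 per group, in the safe direction, and the section announces a conservative approach. The crossover test would have far more than 80% power. Dropout is written with a less-than sign, 100 covers 15% and 16%, and even at 20% the two-group power stays near 82%. The Discussion's remark is a general one about crossover designs and does not say that this trial's size was reduced. Since 42 can be reached with a change-score correlation of about 0.44, one also cannot say that it fits no reading at all.

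Most of this stands, and it sets the size of the point. It does not rescue the text. The unit is wrong as printed, the input that would yield 42 is not stated, and calling the approach conservative does not say that a two-group bound was used for a crossover test. The formula itself is not printed. That it is a two-group one is inferred from the per-group count, the contrast with the standard care group and the absence of any within-person SD or correlation.

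Two stronger readings are tempting and should be resisted. A reader might infer that the trial is underpowered; at SD 5.4 mL/kg/min no primary-outcome calculation above falls below 80% at 40 to 42 per group. A reader might also hold the power claim for biomarkers against the immune-cell and metabolomic work, where "A random subsample of participants (20 subjects in each group" are studied, and apply two-group arithmetic to 20 per group. The section on additional analyses puts that work under the same plan as the primary analysis, which is the crossover, so two-group figures do not describe it. Nor does the Sample size section tie its d of 0.6 to that subsample.

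**Conclusion.** The statement is wrong as written and should be fixed. The SD has no usable unit or type. On the stated inputs, with 5.4 read as mL/kg/min, the requirement is 39 per group rather than 42, and power at 42 is 83.5% rather than 80%. The two-group calculation does not give the power of the planned crossover test, which would be about 98.6% or more with 84 completers. The 100 randomised allow 16% dropout for 84 completers and miss the top of the stated range by five participants (105 − 100), although two-group power would still be about 82% at 20% loss.

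These figures rest on 5.4 meaning mL/kg/min, which only the cited source can confirm. The crossover figures rest also on 5.4 being the SD of a single measurement, on no carryover, and on assumed within-person correlations of 0 or above. The defect is one of justification and reproducibility and gives no reason to change the sample size.

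**What to change.** Keep 100 participants and rewrite the paragraph as follows.

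- Confirm the unit and type of the SD (value, change or within-person difference) against the cited source, and print both.
- State which test the power refers to. For the planned crossover test, give the SD of the within-person difference, or the between-subject SD with the within-person correlation, and restate the power.
- If the two-group figure is kept as a conservative bound, say so, and report about 84% power at 42 per group and about 82% at 40 per group, conditional on an SD of 5.4 mL/kg/min.
- State that 100 randomised allow 16% dropout for 84 completers.
- Restate the secondary-outcome claim on the same basis as the primary one. On a two-group basis, d = 0.6 has 77.6% power at 42 per group, and 80% needs d of about 0.62.

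Do not resolve the mismatch by writing a first-period comparison at week 6 into the paragraph, because the analysis section plans no such primary test.

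The cost is a check of the source and one rewritten paragraph. No participants are added and the analysis does not change.

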#### Methods in analysis to handle protocol non-adherence and any statistical methods to handle missing data

The study follows an intention-to-treat principle with the use of baseline observation carried forward imputation, where the baseline value will replace missing data [61]. The final analysis population will be fully described and differences from the enrolled population will be presented. Cases that are lost may remain in the analysis, although they will provide less information and reduce the variance of estimated effects less than cases that are present for all measurement times. Adherence will be the number of group sessions attended/in sessions completed by each participant divided by the total number of sessions available × 100. Retention will be the number of participants who remained in the training program for all 6 weeks divided by the total number of participants × 100. Satisfactory adherence is defined as a minimum of ≥80% adherence to the prescribed RT sessions. Any discrepancies in data analysis between the methods will be resolved by a third-party biostatistician. First, descriptive statistics for the overall sample and between groups will be calculated. Second, a sequence 1–2 crossover analysis will be conducted using *t* tests and/or ANOVA to determine changes in primary and secondary continuous outcomes with individual participants as blocking factors. Categorical outcome measures will be analyzed using a McNemar test for data combined across both periods of the crossover. In addition, the proportions of participants reporting or not reporting long-term COVID-19 symptoms at the end of each period will be compared using a 2-proportion *z* test. If this test yields a statistically significant result, the usual test for differences between the effects of the two treatments should not be applied. By neglecting carryover effects using the procedure of Gaus and Högel [62], we expect enough power for investigation of differences. All analyses will be 2-sided. An *α* value ≤.05 will be considered to indicate statistical significance for the primary analysis.

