### Procedure

Participants will be randomly assigned (1:1) to one of 2 sequence orders using computer-generated random numbers. All participants will complete both group interventions. Therefore, as participants will act as their own control, this approach will remove any potential differences between subjects and reduce the potential bias when estimating the intervention effect. First, eligible and consenting participants will start with the baseline assessment (T0). Second, participants will be assigned to start 6 weeks of either control group (Sequence 1) or exercise training (Sequence 2), T1 (week 6). Third, full crossover occurred after the 6 weeks, during which participants completed a second 6-week period of the opposite condition (T2, week 12). Outcome assessments will be performed at the end of the immediate intervention and control phase and at the end of the crossover intervention phase (Fig. 1). The general procedure is shown in Fig. 2.

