Exercises	Pectoral press, back press, squat press and knee extension											
Warm up	2 sets of 5 reps at 30–40% of daily maximum strength											
Sets	3	3	3	3	3	3	3	3	3	3	3	3
Repetitions	10	10	12	12	10	10	12	12	8	8	10	10
Intensity (1 RM %)	50	50	50	50	60	60	60	60	70	70	70	70
Cool down												
Stretching	5 min of static and dynamic flexibility exercises											

*1 RM* one-repetition maximum

The no-exercise (control group) will receive standard hospital care, which includes rehabilitation when necessary. Standard care will rigorously conform with all the standard care steps in the current COVID-19 management protocol, and participation will not affect the patients’ treatment or the care they receive during recovery from the disease during the study or in the future. As described at the beginning of the procedure section, this protocol will use a crossover design in which the intervention group will receive the intervention (RT) during the first phase (6 weeks) followed by standard medical care during the second phase (6 weeks). The control group will receive the treatments in the reverse order (standard treatment first followed by the RT intervention). This will allow us to make individualized adjustments, allowing each subject to serve as their own control. If participants desire to stop training and develop health conditions (i.e., SARS-CoV-2 reinfection) or injury that precludes safe participation of exercise over the course of the intervention, we will discontinue training. Participants will be asked to not participate in another structured exercise regimen or intervention over the course of their participation in either the intervention or control group; otherwise, they will not be allowed to continue participation.

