### Outcome measures

The measurements include a medical health interview and examination (e.g., body measures, blood pressure, heart rate, ECG), a V̇O_2_max test, a whole-body dual-energy X-ray absorptiometry (DXA) scan, blood samples, 1-repetition max for upper and lower body muscles, and questionnaires (PROMs: patient-reported outcome measures, physical activity levels, diet recall, quality of life, etc.). The questionnaires will be administered online using SurveyMonkey. Participants will receive an email with a personal link to fill out the questionnaires. For optimal retention, participants will be contacted by the research assistant if they have not completed the questionnaires within 1 week. Outcome measures will be assessed at T0, T1, and T2. See Fig. 2 for the measurements at all time points.

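### Carrying the week-0 value forward biases the two crossover sequences in opposite directions and does not fit the plan's own account of lost cases

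*Protocol article*

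**What the plan says.** The section on non-adherence and missing data (Protocol article, Statistical procedures) declares an intention-to-treat analysis and specifies the "use of baseline observation carried forward imputation, where the baseline value will replace missing data". The analysis it then names is a within-participant crossover comparison by t tests and/or ANOVA.

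The Procedure section defines one baseline only: "First, eligible and consenting participants will start with the baseline assessment (T0", at week 0. It then says that "full crossover occurred after the 6 weeks, during which participants completed a second 6-week period of the opposite condition (T2, week 12". It describes no washout and no separate baseline for the second period. The Outcome measures section adds: "Outcome measures will be assessed at T0, T1, and T2".

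Two sentences after prescribing the imputation, the missing-data section says: "Cases that are lost may remain in the analysis, although they will provide less information and reduce the variance of estimated effects", and the sentence ends by saying that they do so to a smaller degree than complete cases.

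Two statements in the Intervention section bear on who becomes missing. The control group "will receive standard hospital care, which includes rehabilitation when necessary". A further rule asks participants not to take up any other structured programme; it applies "over the course of their participation in either the intervention or control group; otherwise, they will not be allowed to continue participation".

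**The concern.** Baseline carried forward is usually defended in a parallel trial as assuming no benefit for people who leave. In a crossover, T0 precedes both conditions, so the same rule does different things in the two sequences.

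- **Control first, T2 missing:** the exercise-period value is replaced by the week-0 value. The record shows no exercise gain.
- **Exercise first, T2 missing:** the control-period value is replaced by the week-0 value. Natural recovery and any retained training gain disappear from the control condition, so exercise looks better by comparison.

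The net error in the primary estimate therefore depends on who drops out and when. The imputed values are also analysed as if observed. Finally, the section seems to describe two different analyses: one that fills every gap, and one in which incomplete cases count for less. Ending participation for taking up other exercise can add missing values that the imputation then fills.

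**Working it through.** **Inputs from the Sample size section.** True effect τ = 3.5 mL/kg/min; dropout given as below 15–20%; 84 needed and 100 randomized, 50 per sequence. The step from 84 to 100 reproduces: 84/(1 − 0.16) = 100. At 20% loss, 80 remain.

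**Assumptions not in the document.** Natural change π₁, π₂ per period (0 to 1.5 mL/kg/min); carryover λ from exercise into a following control period; within-person correlation 0.5 to 0.9; dropout unrelated to outcome. The SD is printed as 5.4% and is read here as 5.4 mL/kg/min. It affects the standard errors and coverage below, not the biases.

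**Expected contrast, exercise minus control, when everything is observed.**
- Control first: T2 − T1 = τ + π₂
- Exercise first: T1 − T2 = τ − π₂ − λ

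**T2 missing in a share d and set to T0.**
- Control first: T0 − T1 = −π₁, so the bias is −d(τ + π₁ + π₂)
- Exercise first: T1 − T0 = τ + π₁, so the bias is +d(π₁ + π₂ + λ)
- Pooled, equal d: half the sum, −d(τ − λ)/2

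T2 has weight +1 or −1 whether levels or period changes are compared, so these T2-only shifts are the same under either reading.

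**Numbers at d = 0.15–0.20, λ = 0, recovery 0 to 1 per period.**
- Control first: −0.15 × 3.5 = −0.53 to −0.20 × (3.5 + 2) = −1.10
- Exercise first: 0 to +0.20 × 2 = +0.40
- Pooled: −0.15 × 3.5/2 = −0.26 to −0.20 × 3.5/2 = −0.35, which is 7.5–10% of 3.5

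**T1 and T2 both missing.** Every such record has a difference of zero. With λ = 0 the pooled bias is −dτ: −0.53 to −0.70, or 15–20%.

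**Unequal T2 loss.** With d₁ for control first and d₂ for exercise first, the pooled bias is ½[d₂(π₁ + π₂ + λ) − d₁(τ + π₁ + π₂)]. The splits below average 18%; they are assumed, and λ = 0.
- 30%/6%, recovery 0.5: ½[0.06 − 1.35] = −0.645
- 6%/30%, recovery 0.5: ½[0.30 − 0.27] = +0.015
- 6%/30%, recovery 1.5: ½[0.90 − 0.39] = +0.255
- No true effect, 6%/30%, recovery 0.5: ½[0.30 − 0.06] = +0.12; simulated type I error 6.3%
- No true effect, 6%/30%, recovery 1.5: ½[0.90 − 0.18] = +0.36; simulated type I error 17.2%

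With no true effect and equal loss, the simulated type I error was 4.9%.

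**Standard error and coverage.** Simulation of the crossover t test: 50 per sequence, 18% missing, τ = 3.5, recovery 0.5, λ = 0. The observed-data SE uses only participants with both values.

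| Correlation | Missing | Estimate | Reported SE | Sampling SD | Observed-data SE | 95% interval covers 3.5 |
|---|---|---|---|---|---|---|
| 0.5 | T2 | 3.18 | 0.553 | 0.557 | 0.596 | 91% |
| 0.8 | T2 | 3.18 | 0.363 | 0.364 | 0.377 | 87% |
| 0.9 | T2 | 3.19 | 0.272 | 0.269 | 0.266 | 80% |
| 0.5 | T1 and T2 | 2.87 | 0.506 | 0.508 | 0.596 | 76% |
| 0.8 | T1 and T2 | 2.88 | 0.337 | 0.338 | 0.376 | 54% |
| 0.9 | T1 and T2 | 2.87 | 0.257 | 0.260 | 0.266 | 33% |

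The reported SE agrees with the sampling SD of the imputed estimate. It is 4–7% (T2 lost) or 10–15% (both lost) below the observed-data SE at correlations 0.5 and 0.8. At 0.9 it is between 3% below and 2% above. Coverage is lowest at correlation 0.9, where the SEs nearly agree, so the bias is the main cause. The observed-data estimate stays at 3.50.

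**Text against text.** Under baseline carried forward, a lost case has a value at every visit and counts as fully as a complete one. The sentence on less information describes an available-data analysis. Both cannot describe the same primary analysis, and saying that lost cases may remain makes inclusion sound optional under a declared intention-to-treat principle.

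**The case against.** The strongest defence is that the net effect is conservative. With equal dropout and no carryover, the opposite biases partly cancel and leave attenuation, which in a superiority trial does not produce a false positive. The document gives no dropout split by sequence, so the type I error figures rest on an assumed 6%/30% loss and assumed recovery. This stands as far as it goes. But attenuation of the primary estimate is still an error, and the plan contains nothing that ensures equal loss.

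Three stronger readings are tempting and should not be adopted.

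- **A reader might infer that the standard error is simply wrong.** A period-1 comparison invites this: 1.006 with 50 per group after imputation against 5.4 × √(2/42) = 1.178 with 42 completers per group. These are standard errors of two different estimators. The reported one is right for the imputed estimate; it is usually, not always, smaller than the observed data support.
- **A reader might infer that anyone who takes up exercise is dropped from the analysis.** The Intervention section covers another structured regimen or intervention and ends participation. It does not state exclusion from the analysis, and the missing-data section promises to describe how the analysed and enrolled populations differ. What is unclear is whether outcomes are still collected afterwards.
- **A reader might size the problem with change scores and half the gain retained.** That gives (3.5 + 5.25)/2 = 4.375 before any value is lost. The excess over 3.5 is not caused by the imputation, so the example does not isolate it.

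Rehabilitation given within standard care can also be read as not being another regimen. That makes the Intervention point one of reconciling wording, not a proven contradiction. A mixed model could have been left to an analysis plan that is not shown, but this article does not leave the method open: it names the imputation.

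**Conclusion.** The point holds. Replacing missing values with T0 does not suit this crossover: for a missing T2 it biases the control-first sequence against exercise, and the exercise-first sequence towards exercise unless there is neither recovery nor carryover. The pooled effect is attenuated by 7.5–10% if only T2 is missing and by 15–20% if T1 and T2 are both missing. Those figures assume a true effect of 3.5 mL/kg/min, equal 15–20% dropout unrelated to outcome, and no carryover. A bias in favour of exercise is possible but needs heavier loss in the exercise-first sequence together with recovery or retained gain; the documents give neither figure. Interval coverage of the true effect falls mainly because of the bias. The internal conflict between completing every record and giving lost cases less weight rests on the text alone and needs no assumption.

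**What to change.** - Make the primary analysis a likelihood-based mixed model on all observed T0, T1 and T2 values, with period, treatment and sequence, analysed by assigned sequence.
- Keep baseline carried forward as a sensitivity analysis only, and state that the value carried is T0.
- With the mixed model as primary, align the sentence on lost cases with it or delete it, and replace the optional wording about lost cases with a plain statement that all randomized participants are analysed.
- State that the planned T1 and T2 assessments are still collected and analysed when participation in the assigned condition ends.
- Reconcile the Intervention section's statements that control care includes rehabilitation when necessary and that participants in another structured exercise regimen or intervention may not continue.

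The cost is mostly wording, plus a few visits that are already scheduled. The model relies on a missing-at-random assumption, which should be stated. The change does not address carryover, which is a separate matter.
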